## Results

The study is ongoing with results expected in 2017. The expert panel met and reviewed the initial list of risk factors based on the literature review (see Table 1). They made recommendations for additions and deletions and provided insight into where, and in what format, the documentation of the risk factors might exist in the EHR. This list was then iteratively refined through review and discussion with individual experts in the field. The cohort for the study has been identified and all structured, unstructured, and semistructured data have been exported into a relational database for analysis. A description of the cohort is provided in Table 2.

The cohort is almost exclusively male (11,796/12,344, 95.56%), with 68.96% (8513/12,344) being white and 19.64% (2424/12,344) being black or African American. The mean age of the cohort was 58 years (SD 14) with more than half (6782/12,344, 54.94%) being between 50 and 69 years of age. Approximately half (6873/12,344, 55.68%) reported being married.

Annotation schemas have been developed, samples of documents have been extracted, and annotation and adjudication are ongoing. Table 3 outlines the variable targeted through the annotation process.

**Table 2 table2:** Description of study cohort (N=12,344).

Characteristic		n (%)
**Gender**		
	Female	548 (4.44)
	Male	11,796 (95.56)
**Race**		
	Asian	74 (0.60)
	Black or African American	2424 (19.64)
	Native Hawaiian or other Pacific Islander	1 (0.01)
	White	8513 (68.96)
	Other	28 (0.23)
	Unknown by patient/missing	1214 (9.83)
**Ethnicity**		
	Hispanic or Latino	939 (7.61)
	Non-Hispanic or non-Latino	10,723 (86.87)
	Unknown by patient/missing	82 (0.66)
**Age group, years**		
	<21	24 (0.19)
	21-30	491 (3.98)
	31-40	824 (6.68)
	41-50	1854 (15.02)
	51-60	3753 (30.40)
	61-70	3120 (25.28)
	71-80	1540 (12.48)
	81-90	701 (5.68)
	>90	36 (0.29)
	Missing	1 (0.01)
**Marital status**		
	Single/never married	2354 (19.07)
	Married	6125 (49.62)
	Divorced	3097 (25.09)
	Widow/widowed	560 (4.54)
	Unknown/missing	187 (1.51)

**Table 3 table3:** Pressure ulcer (PrU) annotation schemas.

Task	Variable	Attributes	Description	Example text spans
Annotation task 1	Pressure ulcer	Pressure ulcer	Text indicating presence of a PrU	Pressure ulcer, skin sore, decubitus ulcer
		Stage	Stage of the PrU	Stage 1, stage 2, unable to stage, stage 3-4
		Laterality	Right, left, bilateral, midline, not applicable, unspecified	Right, left, lower extremity
		Location	Anatomic location of PrU	Coccyx, heel, trochanter, sacrum, ankle, ischial
		Orientation	Medial, lateral, proximal, distal, dorsum, plantar, anterior, superior, posterior, inferior, unspecified	Bilateral
		Temporality	Date: date of examination Duration: span of time since PrU discovered	Sept 10, 2009, approximately one year
		Assertion	Modifiers: historical, recurrent, negated, hypothetical, not PrU, unspecified	Healed pressure ulcer, history of pressure ulcers, no pressure ulcers, if pressure ulcers develop
	Noncompliance	None	Documentation of noncompliance with pressure release	Patient refuses to turn because of pain
	In label	None	PrU mentions within section labels in documents (ie, are not indications of a PrU)	Pressure ulcer protocol Pressure ulcer education
Annotation task 2	Living situation (LS)	LS cue	Key phrase indicating presence of LS	Living at, living with, address, living arrangements
		LS main	Actual value assigned to LS (ie, alone, nuclear family, extended family, roommate, group, homeless)	Mother’s residence, girlfriend, half way house, caregiver, spouse
	Malnutrition (MN)	MN cue	Key phrase indicating presence of MN	Nutrition status:
		MN main	Actual value assigned to MN	Moderately compromised, severely compromised
	Moisture (MO)	MO cue	Key phrase indicating statement about MO	Moisture: Constantly moist:
		MO main	Text indicating presence of MO (ie, fecal, urinary, sweat)	Multiple loose stools, copious amounts foul purulent drainage, night sweats, perspiration, urine
		Assertion	Modifiers: asserted, historical, hypothetical, negation, not patient, uncertain	Was, prior medical history, nutrition risk, manage, []^a^, history of
Annotation task 3	Template components	Header	Title line naming the template	Braden Scale, ASIA^b^ score
		Item label	Label for individual assessment items	Moisture, turgor, color, temp
		Item score	Value (text or number) assigned to item	Moist, red, 4, 0
		Total label	Text identifying the summed score	Total score:
		Total score	Final value for the assessment	30, high risk
		Whole template	Offsets from block of text identifying template boundaries	132-165

^a^These empty brackets would be generated by the system and placed in a progress note when a check box was left blank in a template in the electronic medical record system.

^b^ASIA: American Spinal Cord Injury Association.

The annotation process was split into three tasks to allow for sampling of different types of documents, depending on the targeted variables. This also reduces the cognitive burden for the annotators in each of the tasks. In the first task, the emphasis is on identifying attributes of the pressure ulcers and on any documentation of patient noncompliance with steps to reduce pressure ulcers, such as pressure release. In the second task, the primary targets were the patients’ living situation, whether there was any evidence of malnutrition, and whether there was evidence of ongoing moisture on the skin. Annotation for each of the targeted variables included both a *cue* (phrase indicating presence) for the variable and the actual value assigned to the variable. The third annotation task was slightly different in that it emphasized labeling of the structural component of semistructured text (stored in templates). This information will allow for targeted extraction of the information contained in the template. Operational definitions of ICD-9-CM codes are being created. Once all of the various data are defined and extracted, they will be combined into an analytic dataset for development of risk models.

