### Aims and Hypotheses

The goal of this study is to develop an improved SCI PrU risk model to better predict level of risk, guide preventive practices, and ultimately maximize the patient’s clinical outcomes. The resultant risk model, tailored to veterans with SCI, should promote adoption into clinical practice.

We will test two hypotheses to compare a model based on the commonly used Braden Scale versus (1) a risk model developed using structured data alone and (2) a model using both structured and NLP (ie, semistructured and unstructured) data. A third hypothesis will test the added value of NLP-based data over structured data. The hypotheses are as follows:

1. Hypothesis 1: The risk model using structured data alone will predict the development of PrUs better than the model based on the Braden Scale.

2. Hypothesis 2: The risk model based on combined structured and NLP data will predict the development of PrUs better than the model based on the Braden Scale.

3. Hypothesis 3: The risk model based on combined structured and NLP data will predict the development of PrUs better than the model based on structured data alone.

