### Variables Selection and Definition—Ongoing

The dependent variable for this study will be documentation of the occurrence of a PrU in the EHR within 1 year (ie, 1-year incidence risk of PrU). The definition of the presence of a PrU used for case identification is based on ICD-9-CM codes (707.0-707.9) and the application of the classification algorithm based on text analysis or a combination of these two sources, depending on what is found to be more accurate. The potential independent variables for this study include the risk factors that were identified through a literature review and validated by expert panel discussion. The final list of potential risk factors, with input from the expert panel, will be extracted from multiple tables in the EHR, or from semistructured and unstructured text notes, for use in analysis. Three sets of candidate predictors based on data sources will be generated to develop each risk model: (1) structured data extracted directly from the EHR, (2) Braden scores, and (3) a combination of existing structured data and data extracted from text through the NLP processes.

The investigators conducted a comprehensive literature review generating a list of approximately 50 potential independent variables or risk factors (eg, demographics, diseases status, comorbidities, health behaviors, psychosocial factors, and home care). This list was reviewed by the expert panel for logical consistency, completeness, clinical relevance, and whether they were modifiable or not. The panel identified high-priority risk factors and discussed practical considerations including where the risk factor might be located in the EHR, how reliable these data might be, and alternative ways to document risk factors. Subsequently, persistent moisture on the skin, the type of living situation of the patient, evidence of malnutrition, and documentation that the patient took steps to redistribute their weight during the day were targeted as risk factors available in unstructured data. Structured data contained elements of the Braden Scale, lab values, and other variables (see Table 1). Several coding systems are used to classify structured data variables, including the ICD-9-CM, Logical Identifiers Names and Codes (LOINC), and the Healthcare Common Procedural Coding System (HCPCS). International Classification of Diseases, Tenth Revision, Clinical Modification (ICD-10-CM) codes were not implemented in the VHA until after the end of this study and are not used.

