	VHA-issued equipment	HCPCS^d^ codes for wheelchair cushion, bed support surface, and other equipment
	Telehealth	Distant observation of skin integrity
Semistructured	Motor/sensory assessment	American Spinal Cord Injury Association (ASIA) classification of SCI^e^ (eg, ASIA A= *Complete* injury of spinal cord)
	Level of injury	Cervical (C1-C8), thoracic (T1-T12), lumbar (L1-L5), and sacral (S1-S5)
	Alcohol use	Alcohol Use Disorders Identification Test—Consumption (AUDIT-C)
	Tobacco use	Current/former/nonsmoker
	Caregiver resources	Receiving aid and attendant, VHA-supported/reimbursed bowel/bladder care
	Duration of SCI	Years since injury/onset
	Sensation^f^	Ability to feel and relieve discomfort
	Moisture^f^	Exposure to moisture on trunk (ie, bowel/bladder leakage/accidents due to management or lack of containment, diarrhea, and diaphoresis)
	Mobility^f^	Ability to relieve pressure on high-risk areas (eg, trunk and heels)
	Activity^f^	Level of activity (ie, ability to get out of bed and ambulation)
	Nutrition^f^	Food intake malnutrition, undernutrition, and moderate/severe compromise
	Friction and shear^f^	Ability to minimize resistance between two parallel surfaces (ie, bed linens and skin)
	Living situation	Living arrangements (eg, alone, immediate family, extended family, roommate, and group setting)
Unstructured	Noncompliance with pressure redistribution	Patient refusal/decline to turn in bed
	Pain	Numeric pain rating scale (1-10) when pressure ulcer develops
	Pressure ulcer history	Previous pressure ulcer

^a^VHA: Veterans Health Administration.

^b^ICD-9-CM: International Classification of Diseases, Ninth Revision, Clinical Modification.

^c^LOINC: Logical Identifiers Names and Codes.

^d^HCPCS: Healthcare Common Procedural Coding System.

^e^SCI: spinal cord injury.

^f^Element of the Braden Scale.

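### One moisture example span in Table 3, purulent drainage, contradicts the article's own definition of moisture and could let a sign of an existing ulcer into the combined structured-plus-NLP model

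*Protocol article*

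**What the plan says.** Table 1 lists moisture as a semistructured risk factor, footnotes it as a Braden element, and defines it as "Exposure to moisture on trunk (ie, bowel/bladder leakage/accidents due to management or lack of containment, diarrhea, and diaphoresis".

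Table 3, annotation task 2, describes the value to be tagged for moisture (MO main) as "Text indicating presence of MO (ie, fecal, urinary, sweat". In the same row, the example spans are "Multiple loose stools, copious amounts foul purulent drainage, night sweats, perspiration, urine". The qualifiers that an annotator can attach to a moisture mention are "Modifiers: asserted, historical, hypothetical, negation, not patient, uncertain".

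Methods, Variables Selection and Definition, names among the text targets "persistent moisture on the skin, the type of living situation of the patient, evidence of malnutrition", and says that these targets "were targeted as risk factors available in unstructured data". The three predictor sets are given there as "1) structured data extracted directly from the EHR, (2) Braden scores, and (3) a combination of existing structured data and data extracted from text". Hypothesis 2 reads "The risk model based on combined structured and NLP data will predict the development of PrUs better than the model based on the Braden Scale". Hypothesis 3 makes the same claim for the combined model against structured data alone.

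**The concern.** Four of the five example spans fit the stated sources: loose stools, night sweats, perspiration and urine. The fifth is pus. It fits neither closed list, so the schema instructs annotators to do something that the definition rules out.

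This matters because of what the study predicts. Foul purulent drainage is a natural description of an infected ulcer, and the outcome is an ulcer. If drainage from an ulcer already present is recorded as moisture, a consequence of the outcome sits among its predictors. The moisture coefficient would then be too large, moisture would rank too high in the risk-factor lists meant for clinicians, and some of the apparent value of the text data would not be real. Free-text extraction feeds only the third predictor set, so any distortion from this span falls on Hypotheses 2 and 3 and leaves Hypothesis 1 untouched.

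**Working it through.** **1. The definitions side by side**

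| Place | Sources of moisture | Purulent drainage included? |
|---|---|---|
| Table 1, Moisture | bowel or bladder leakage, diarrhea, diaphoresis | no |
| Table 3, MO main, description | fecal, urinary, sweat | no |
| Table 3, MO main, examples | stool, sweat, urine, purulent drainage | yes |

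Both definitions use *ie*, which closes the list.

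**2. Would a later step catch it?** None of the six moisture modifiers concerns the source of the fluid. The pressure-ulcer row, by contrast, has a modifier for mentions that are not an ulcer. Adjudication by a third clinician (Step 1) settles disagreements under the same schema. The 70/30 document check (Step 2a) scores the pipeline against that reference standard, so extracted drainage would count as correct.

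**3. Could an ulcer be present but uncoded?** Sample and Sampling reports 3860 ulcers from structured data and 829 from text alone.
- 3860 + 829 = 4689, and 4689/12,344 = 37.99%, which reproduces the article's figure.
- 829/4689 = 17.7% of ulcers were seen in text only.
- Freedom from ulcer at baseline was judged from ICD-9-CM codes only.

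So an uncoded ulcer can be present when drainage is charted. The article states no rule that a text-derived predictor must predate the ulcer.

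**4. Illustrative size.** Every flag rate and base AUC below is an assumption. Let the base score be normal with unit variance and shifted by μ = √2·Φ⁻¹(base AUC) in cases. Let a binary flag, independent of the score given outcome, have rate p1 in cases and p0 in non-cases. With the flag weighted optimally,

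AUC = Σ w1·w0·Φ[(μ² + m1 − m0)/(μ√2)],

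where m is ln(p1/p0) if flagged and ln[(1−p1)/(1−p0)] if not, w1 and w0 are the matching probabilities, and the sum runs over the four combinations.

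*(a) Drainage pooled into moisture, as the schema would do.* True moisture is set at 20% in everyone with no effect. Drainage flags a further share q of otherwise unflagged cases and no non-cases. Then p0 = 0.20, p1 = 0.20 + 0.80q, and the spurious odds ratio is [p1/(1−p1)]/(0.20/0.80).

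| q | p1 | Odds ratio | AUC gain, base 0.752 | AUC gain, base 0.65 |
|---|---|---|---|---|
| 5% | 0.24 | 1.26 | 0.001 | 0.002 |
| 10% | 0.28 | 1.56 | 0.004 | 0.008 |
| 20% | 0.36 | 2.25 | 0.014 | 0.028 |

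*(b) Drainage as its own flag, with some non-cases flagged.* Base AUC is 0.65 to 0.75, with 200 simulated validation samples of n = 3703 (0.30 × 12,344 = 3703.2, the article's validation size). The last two columns give the share of runs in which the DeLong z for the AUC difference exceeded 1.96. The 10% outcome rate is assumed, and 38% is the study-period incidence.

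| Flag rate, cases vs non-cases | AUC gain | z > 1.96, outcome 10% | z > 1.96, outcome 38% |
|---|---|---|---|
| 1% vs 1% | 0.000 | 0% | 0% |
| 2% vs 1% | 0.001–0.002 | 2.5–3% | 18.5–21.5% |
| 5% vs 1% | 0.006–0.011 | 39.5–64% | 91.5–99.5% |
| 10% vs 1% | 0.019–0.029 | 98–100% | 100% |

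At base AUC 0.70 and 10% vs 1%, mean sensitivity over false positive rates of 0 to 0.10, the type of region to which the plan gives priority, rises from about 0.17 to 0.23. A more extreme pair, 20% vs 2%, gave 0.037 to 0.059. It is left out of the stated range because it needs drainage notes in one case in five and is not diluted by true moisture.

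**The case against.** The strongest reply is that this is one of five illustrative spans and that the rest is inference. Much of that stands.

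- The span names no wound, ulcer or body site. That the drainage comes from an ulcer is plausible but not stated.
- The text on variable selection speaks only of persistent moisture on the skin and does not limit its source. The conflict is therefore with Table 1 and the Table 3 description, not with that section.
- Drainage from the outcome ulcer leaks only if notes from its onset or later are used. The exact predictor window is a detail that an article may leave to the full protocol. If predictors must predate the ulcer, an earlier uncoded ulcer is the remaining route.
- Moisture is also a Braden item, and annotation task 3 targets Braden templates, so moisture recorded in text can reach the Braden comparator too. Only the free-text drainage span is confined to the third predictor set.
- The structured set has items tied to the outcome as well: inpatient or outpatient status at ulcer onset, and surgery in the six months before it.
- Moisture must still survive model selection, and calculation (a) puts every drainage flag in cases, which is the worst case.

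A reader might infer that the schema demonstrably tilts Hypotheses 2 and 3 towards the combined model, or that moisture reaches that model alone. The documents support neither reading, for the reasons above. What the reply does not remove is the contradiction inside Table 3 and with Table 1, or the fact that no described step would correct it.

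**Conclusion.** The inconsistency is certain: the example contradicts its own row and Table 1, and applying it as written would code purulent drainage as moisture. The consequence is a risk, not a demonstrated bias. A sign of an existing, possibly uncoded, ulcer could enter the combined model through this span and could favour it in Hypotheses 2 and 3. The net direction and size cannot be determined from the documents. Illustrative AUC gains run from about 0 to 0.03. They rest on assumed flag rates and base AUCs, on drainage being more frequent in cases, and on the text data carrying no other information. If drainage notes are rare or unrelated to the outcome, the effect is negligible. At n = 3703, however, a gain of about 0.01 would often reach significance, which justifies an inexpensive correction.

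**What to change.** In Table 3, remove the drainage example from MO main, or move purulent and wound drainage to a separate class that is kept out of the moisture predictor. State the exclusion in the schema, so that MO main covers the same sources as Table 1. Then search the moisture spans already tagged for drainage and purulence terms, and re-adjudicate those before the NLP rules are fixed.

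The cost is a one-line schema edit, a keyword search and slight re-adjudication, with no new documents to sample. Results describes annotation and adjudication as ongoing, although Methods heads the reference-standard step as complete. If that step has in fact closed, the same search applies to the finished corpus and the rules must be refitted on the corrected labels. The moisture effect may come out weaker.

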## Discussion

When completed, the results of this study will provide clinicians in the VHA system with a PrU risk assessment model specific to veterans with SCI. As part of the study, the predictive ability of the new model will be compared directly with that of the Braden Scale, the current risk assessment. Also, individual items on the Braden Scale will be tested for inclusion in the model. This will provide clinicians with information about the clinical utility of the new model. Initially, the new model will be distributed in the form of a simple stand-alone desktop computer program; however, our long-term goal is to deploy the risk assessment as an automated, integrated part of the VHA EHR. Clinicians could use the improved risk model to (1) maximize the impact of expensive resources for prevention of PrU (eg, specialty mattress and paid caregiver) by identifying those veterans at highest risk, (2) justify allocation of staffing resources (eg, home health care or telehealth), and (3) institute policies (eg, frequency of turning the veteran in bed). Further, we believe this study represents a model of how to leverage information from the EHR for risk assessment that could be applied to other clinical problems.

## Abbreviations

AHRQ: Agency for Healthcare Research and Quality
AORTIS: Aggregation, Organization, Reduction, Transformation, Interpretation, and Synthesis
ASIA: American Spinal Cord Injury Association
AUC: area under the curve
AUDIT-C: Alcohol Use Disorders Identification Test—Consumption
EHR: electronic health record
FY: fiscal year
GAM: generalized additive model
GATE: General Architecture for Text Engineering
HCPCS: Healthcare Common Procedural Coding System
HCUP: Healthcare Cost and Utilization Project
hx: history
ICD-9-CM: International Classification of Diseases, Ninth Revision, Clinical Modification
ICD-10-CM: International Classification of Diseases, Tenth Revision, Clinical Modification
IE: information extraction
info: information
LOINC: Logical Identifiers Names and Codes
LS: living situation
MN: malnutrition
MO: moisture
NLP: natural language processing
pAUC: partial area under the curve
PrU: pressure ulcer
PrU+: presence of a pressure ulcer
PrU-: absence of a pressure ulcer
ROC: receiver operating characteristic
SCI: spinal cord injury
SCI/D: Spinal Cord Injury and Disorder
VHA: Veterans Health Administration
VINCI: Veterans Affairs Informatics and Computing Infrastructure
VSSC: VHA Support Service Center
